# Investigating environmental heat exposure and its effects on maternal and fetal health in rural Northern Ghana (Physio-HeMAB Study): a study protocol for a cluster randomized trial

**DOI:** 10.1186/s12889-026-28030-8

**Published:** 2026-07-06

**Keywords:** Heat, Heat stress, Pregnancy, Physiology, Fetal health, Wearable sensors, Physiological monitoring, Climate change adaptation

## Abstract

**Background:**

Climate change increases the frequency and intensity of heat events. Previous studies have established a correlation between heat exposure and adverse pregnancy outcomes, including preterm birth, stillbirth, and other maternal and fetal health complications. However, evidence on the physiological pathways underlying heat strain during pregnancy and on whether heat adaptation strategies can modify these responses remains limited, particularly in low-resource settings. This study aims to assess the effects of environmental heat exposure on maternal and fetal physiological responses among pregnant women exposed and unexposed to a heat adaptation strategy.

**Methods:**

Physio-HeMAB is an interventional, cluster-randomized study hosted by the Health and Demographic Surveillance System in Navrongo, Ghana. This study integrates: (i) high-resolution environmental monitoring including Wet-Bulb Globe Temperature at household level and Universal Thermal Climate Index environmental data at regional level; (ii) continuous maternal physiological assessment via wearable devices measuring heart rate, heart rate variability, core body temperature, physical activity, and sleep; and (iii) fetal health assessments, including fetal heart rate and Doppler indices. This multimodal framework supports detailed assessment of how varying levels of environmental heat exposure relate to maternal physiological changes and fetal health indicators. Descriptive and multivariable statistical methods will be used to analyze the data.

**Discussion:**

A better understanding of the physiological mechanisms of heat strain during pregnancy, and an evaluation of whether targeted adaptation strategies can mitigate its effects, are essential for protecting maternal and neonatal health. This Physio-HeMAB study integrates individual-level physiological responses to environmental heat exposure and heat adaptation strategies. This approach strengthens the evidence for developing context-specific and gender-responsive public health interventions.

**Trial registration:**

This study was registered in the Pan African Clinical Trials Registry as PACTR202601761543866 on 05 January 2026.

**Supplementary Information:**

The online version contains supplementary material available at 10.1186/s12889-026-28030-8.

## Introduction

The climate crisis is widely recognized as one of the biggest global health threats of the 21st century [1]. Climate change acts as a “threat multiplier”, intensifying existing social, economic, and health inequalities, and disproportionately impacting vulnerable populations [2]. Pregnant women are especially affected due to intersecting structural inequalities and limited access to adaptation resources, particularly in regions with fragile health systems. This highlights the critical connection between climate resilience and gender equality [3, 4].

The increasing frequency and intensity of extreme weather events, particularly heatwaves, is a leading cause of weather-related deaths worldwide and represents one of the most urgent concerns facing the global community today [5–7]. Sub-Saharan Africa (SSA) is particularly vulnerable to the complex effects of climate change [8–11]. Ghana, in West Africa, along with many countries in SSA, has experienced an increase of extremely hot days that threaten maternal and newborn health [12]. According to Climate Central, 75% of the pregnancy-related heat-risk days in Ghana are directly attributable to human-induced climate change [12]. Projections from the World Meteorological Organization indicate that this trend will intensify in the coming years [13].

SSA already accounts for nearly two-thirds of the worldwide maternal deaths annually [14–16], and the region experiences a disproportional share of global preterm births [17]. This trend may worsen, as exposure to extreme heat is strongly associated with adverse pregnancy outcomes. A meta-analysis published by Lakhoo et al. in Nature Medicine reported that higher heat exposure is associated with 29% higher odds of low birth weight compared with lower heat exposure. Similarly, short-term heat exposure was associated with a 4% increase in the odds of preterm birth per 1 °C rise and a 26% increase during heat waves [18]. Notably, late preterm birth has been associated with increased temperature exposure during gestational weeks 34–37, suggesting a critical heat-sensitive period in the final weeks of pregnancy [19]. Lakhoo et al. reported increased odds of stillbirth (OR = 1.13) and gestational diabetes mellitus (OR = 1.28) with high heat exposure, and a 25% increase in obstetric complications during heat waves [18].

The biological nature of pregnancy increases vulnerability to heat-related health risks [18, 20, 21]. Pregnancy involves substantial cardiovascular adaptations required to meet the metabolic and circulatory demands of the growing fetus [22–24]. These adaptations are largely regulated by the maternal autonomic nervous system (ANS). Evidence from Bester et al. suggests that advancing gestation is associated with attenuated autonomic responsiveness and reduced system complexity [22]. This potentially reflects a stable and tightly regulated ANS necessary to maintain physiological balance during pregnancy. However, the reduced autonomic flexibility may limit the maternal capacity to rapidly respond to external environmental stressors such as heat exposure [22]. Pregnancy is accompanied by further physiological and anatomical changes, including greater metabolic heat production due to fetal growth, a higher BMI, and a reduced surface area-to-mass ratio [25]. Therefore, the body’s thermoregulatory capacity to maintain core body temperature (CBT) within the narrow range of 37 ± 0.5 °C could be compromised, making it harder to dissipate heat [25]. During heat exposure, increased sweating (i.e., increased loss of body fluids) and inadequate fluid intake may lead to dehydration. This can cause electrolyte imbalances and endocrine disruption potentially triggering premature onset of labor [21]. Additional pathways, including altered glucose metabolism, inflammatory responses, impaired placental development, and disrupted maternal blood flow are hypothesized to contribute to adverse pregnancy outcomes [21, 22, 26–29].

The use of research-grade wearable devices (“wearables”) and environmental data loggers facilitates detailed assessment of such physiological responses to heat exposure under real-world conditions [30–32]. The feasibility and acceptability of wearable technologies have been demonstrated in rural African settings, supporting their use for longitudinal monitoring during pregnancy [30, 33]. Beyond indicators of the maternal ANS such as heart rate and heart rate variability, wearables can be used to estimate physical activity patterns and sleep characteristics [31, 34–36] both of which are relevant pathways through which heat exposure may affect maternal well-being.

Among pregnant women, heat exposure has, for example, been associated with sleep disturbances, fatigue, and heat-related illness, particularly in contexts of strenuous physical labor and where homes cannot be adequately cooled [37, 38]. These impacts are further intensified by gender norms and gendered divisions of labor, which can constrain the support available to pregnant women within households and mean that unpaid domestic and small-holding farm work is continued, even during periods of extreme heat [37, 39]. Limited social and material resources available to women further compound vulnerability during pregnancy [39, 40].

In Ghana, initial steps have been taken to build a climate-resilient health infrastructure. The National Climate Change Policy identifies “Focus Area 3: Increase resilience of vulnerable communities to climate-related risks”, specifically recognizing women as a vulnerable group and outlining actions to strengthen community resilience [41]. Other Ghanaian policies and plans also aim to integrate climate risks into the health sector. Despite these initial efforts, the implementation of climate change adaptation strategies in policies and national plans remains incomplete, and mainstreaming has been limited by insufficient coordination and information systems, as well as inadequate financing [42]. Although women are recognized as a vulnerable group [41], pregnancy and its unique vulnerabilities are often overlooked by policymakers and program implementers in Ghana, reflecting a broader trend observed across many low-resource settings [20, 34, 35].

This highlights the urgent need for an evidence-based, gender-transformative adaptation strategy. Physio-HeMAB specifically evaluates the physiological maternal and fetal response in individuals exposed and not exposed to such a heat adaptation strategy. To achieve this, it adopts a multi-level data collection design, combining environmental heat exposure measurements, continuous maternal physiological monitoring using wearables, and fetal health assessments in an integrated approach.

## Methods and analysis

### Study objectives

Physio-HeMAB study has the following objectives:

Primary objective: to assess the effect of heat exposure (with and without the heat adaptation strategy) on (1) maternal heart rate as a proxy for maternal heat strain.

Secondary objectives: to assess the effect of heat exposure (with and without the heat adaptation strategy) on (1) maternal heart rate variability and (2) physiological strain index as further proxies for maternal heat strain, (3) maternal sleep duration, (4) maternal physical activity, and (5) on fetal strain during assessments.

### Study setting

This study is set in Ghana, a lower-middle-income country in West Africa, which has a tropical climate and annual mean temperatures between 26 °C in the south and 29 °C in the northeast [43]. More specifically, this study will be conducted in the Upper East Region (UER), in the area covered by the Navrongo Health and Demographic Surveillance System (HDSS), run by the Navrongo Health Research Center (NHRC). It is the hottest part of the country, with temperatures reaching up to 40 °C during the dry season lasting from November until April [44]. Climate data indicates a national average temperature rise by 1 °C, with the greatest rate of change in the UER with increases estimated at 2.0–2.5 C° [45].

The HDSS, which monitors approximately 172,000 individuals (52.3% female) and 38,400 households in the two Kassena-Nankana districts, records approximately 4,000 births annually [46, 47]. A network of Community Key Informants, supported by official birth registration systems, ensures the timely collection of data on pregnancies and births [47].

The study will be conducted during the dry season, when mean monthly daytime temperatures are expected to range between 35.5 °C and 38.8 °C [44].

### Study design

Physio-HeMAB is an interventional, cluster-randomized substudy embedded within the larger parent HeMAB trial (PACTR202510765394928). In the parent trial, the heat adaptation strategy (intervention) is allocated to 16 health centers (HCs) through cluster randomization. The primary outcome of the larger HeMAB study is the change in birth weight, assessed in the 3,200 births annually in the study area (*n* = 1,600 per cluster).

Physio-HeMAB does not conduct randomization itself; however, it uses the pre-existing randomized allocation within the existing trial framework to evaluate intervention effects on physiological outcomes. Therefore, by definition, Physio-HeMAB constitutes an interventional study with a cluster-randomized design. The HeMAB study design is visualized in Fig. 1.

**Fig. 1 Fig1:**
[figure not shown]
Overview of the Physio-HeMAB study nested within the larger healthy mamas and babies (HeMAB) trial

Within this framework, Physio-HeMAB applies prospective physiological monitoring to assess maternal and fetal responses to environmental heat in both intervention and control clusters. Each Physio-HeMAB cluster comprises two health facilities (one hospital and one affiliated health center), purposefully selected to ensure comprehensive data collection. At the hospital level, permanent gynecologists perform ultrasound examinations, with support from midwifery staff. The associated health centers are operated by trained midwives who deliver essential maternal and reproductive health services.

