### Sample size and selection of subjects

The sampling method will be consecutive sampling of women who visit any of the four purposefully selected HDSS health facilities for antenatal consultations. Consideration will be made for pregnant women who can conveniently attend the health facility at least three times during the physiological measurement period. Inclusion criteria are (1) being a pregnant woman in the third trimester (> 28 weeks) with a (2) singleton pregnancy. Further inclusion criteria are (3) being of legal age, (4) able to give consent, (5) registration (having an ANC card) and (6) living within 10 km proximity of one of the four selected HDSS health facilities. Exclusion criteria are (1) illness that requires hospital admission or immediate delivery, (2) known fetal malformations, and 2) a known psychological or mental health concern.

The primary outcome variable is maternal heart rate (beats per minute, bpm), which serves as a physiological proxy for maternal heat strain, reflecting cardiovascular responses to heat exposure. To determine an appropriate sample size for the Physio-HeMAB study, a power analysis was conducted for comparing mean heart rates between two independent groups. Assuming a mean detectable difference of 5 bpm, a common standard deviation of 10 bpm, a two-sided significance level (α) of 0.05, and 80% statistical power, the required sample size is 63 per group. The study will enroll 200 participants in total across the four HDSS health facilities, 100 in the intervention group and 100 in the control group. As this is the first time this type of study will be conducted in this setting, it is not yet possible to precisely estimate potential attrition, data loss and inter-individual variability. Therefore, the sample size is chosen to provide a conservative margin, ensuring that even with 30% attrition, the study retains adequate power to detect clinically relevant differences in heart rate between groups.

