## Discussion

Physio-HeMAB is a comprehensive, non-invasive, multi-level physiological assessment designed to capture the complex interplay between environmental heat exposure, maternal physiological responses, and fetal health during pregnancy. A key strength of the study is the integration of continuous environmental monitoring, wearable-based maternal physiological measurements, and fetal assessments within a single analytic framework. Conducting the study within the Navrongo HDSS enables data collection under real-world living and working conditions, enhancing ecological validity and policy relevance. As a sub-study embedded within the larger HeMAB parent trial, Physio-HeMAB leverages the cluster-randomized implementation of a gender-transformative heat adaptation strategy to compare physiological responses between exposed and unexposed participants. This design strengthens the study’s relevance for adaptation policy by linking physiological evidence to a real-world public health intervention. Importantly, the study addresses a critical evidence gap, as most existing heat-related interventions and early warning systems are not tailored to pregnant women, and physiological evaluations of adaptation strategies in this population remain scarce.

Limitations include that the seven-day monitoring period per participant may not fully capture longer-term variability in heat exposure, behavioral adaptation, or physiological responses. Operationally, Physio-HeMAB is the first study of its kind conducted in this specific setting and with pregnant women. As such, uncertainties remain regarding participant retention, data completeness, inter-individual variability, and the performance of the multiple wearables and environmental sensors under field conditions. To address these challenges, the study deliberately enrolls a larger sample than required for the primary outcome, implements retention-enhancing procedures, and applies rigorous data quality control protocols.

Physio-HeMAB is designed to generate valuable methodological and physiological insights. By linking individual-level physiological responses to environmental heat exposure and adaptation strategies, the study supports the evidence base for the development of context-specific, gender-responsive, and scalable public health interventions aimed at protecting maternal and fetal health in a warming climate.

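### With one purposively selected hospital/health-center pair per arm, the intervention effect cannot be separated from area differences, and the stated power holds only for independent women

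*Protocol article*

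**What the plan says.** Under Study design, the article explains that in the parent trial "the heat adaptation strategy (intervention) is allocated to 16 health centers (HCs) through cluster randomization". It adds that "Physio-HeMAB does not conduct randomization itself" but uses the parent allocation to evaluate intervention effects, and concludes: "Therefore, by definition, Physio-HeMAB constitutes an interventional study with a cluster-randomized design".

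The text after Fig. 1 says that monitoring takes place "in both intervention and control clusters" and defines the sub-study's units: "Each Physio-HeMAB cluster comprises two health facilities (one hospital and one affiliated health center), purposefully selected to ensure comprehensive data collection".

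Under Sample size and selection of subjects, women are sampled consecutively from "any of the four purposefully selected HDSS health facilities for antenatal consultations". The total is then fixed: "The study will enroll 200 participants in total across the four HDSS health facilities, 100 in the intervention group and 100 in the control group". The sample size is a comparison of mean heart rate between two independent groups: difference 5 bpm, SD 10 bpm, two-sided alpha 0.05, 80% power, 63 per group. The article says that power remains adequate with 30% attrition.

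Statistical methods plans linear mixed models with random intercepts, time-varying and participant-level covariates, and a test of the intervention-by-heat interaction.

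The Discussion presents it as a strength that the sub-study "leverages the cluster-randomized implementation of a gender-transformative heat adaptation strategy to compare physiological responses between exposed and unexposed participants". Its limitations cover the short monitoring period, retention, data completeness, variability between women and device performance. They mention neither the number of clusters nor the purposive selection.

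**The concern.** Randomizing clusters protects a comparison by replication: over many units, area characteristics tend to balance, and the spread between units within an arm shows how large a chance imbalance could be. One hand-selected pair per arm gives neither. Any difference in heart rate between the two areas is then intervention effect plus area effect, and the data cannot say how much is which. The same applies to a difference between arms in the heat to heart-rate slope.

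The article nevertheless presents the between-arm contrast as a cluster-randomized evaluation, powers it as if the women were independent, and offers the results to inform adaptation policy. The risk is that a difference between two localities is reported as a randomized effect of the strategy, with a p-value that is too small.

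**Working it through.** **Inputs from the article.** Four facilities; two per cluster; both arms present; 100 women per arm; difference 5 bpm; SD 10 bpm; two-sided alpha 0.05; 80% power; 30% attrition. The article gives no intracluster correlation (ICC), so 0.01, 0.02 and 0.05 are assumed throughout.

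**1. The planned figure reproduces.** n per group = 2 × (1.960 + 0.842)² × 10² / 5² = 62.8, rounded up to 63. For independent women, power is 94% with 100 per arm and 84% with 70 per arm (30% lost). The arithmetic is right for that setting.

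**2. Number of clusters.** 4 facilities / 2 per cluster = 2 clusters. With both arms present, that is k = 1 per arm. Between-cluster degrees of freedom = 2(k − 1) = 0. No cluster-level standard error or test exists, whatever the number of women. A random intercept per woman does not address this, and a random effect for site cannot be separated from arm when each arm is one site.

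**3. Cost of an individual-level test.** Design effect DE = 1 + (m − 1) × ICC with m = 100. True type I error of a nominal 5% test = 2 × [1 − Φ(1.96/√DE)].

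| Assumed ICC | DE | Effective n per arm | True type I error |
|---|---|---|---|
| 0.01 | 1.99 | 50 | 16.5% |
| 0.02 | 2.98 | 34 | 25.6% |
| 0.05 | 5.95 | 17 | 42.2% |

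With 70 per arm, the type I error is 13.2%, 20.4% and 35.3%.

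**4. Size of the area difference alone.** With no intervention effect and no sampling error, the true difference between two single clusters has SD = 10 × √(2 × ICC).

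| Assumed ICC | SD (bpm) | 95% range (bpm) | Chance of exceeding 5 bpm either way |
|---|---|---|---|
| 0.01 | 1.41 | ±2.8 | about 0.04% |
| 0.02 | 2.00 | ±3.9 | about 1.2% |
| 0.05 | 3.16 | ±6.2 | about 11% |

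Steps 3 and 4 treat the two areas as random draws. Purposively selected areas need not behave that way, so the figures show scale only.

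**5. Other readings of the word cluster.**
- *Cluster means arm.* The parent-trial text seems to use it so: 3,200 births at 1,600 per cluster gives 2. Each arm is then still one hospital/health-center pair.
- *Each facility is a cluster.* This gives two per arm and 2(2 − 1) = 2 degrees of freedom. With m = 50, DE = 1.49, 1.98 and 3.45, SE = 10 × √(2 × DE/100), and a noncentral t on 2 degrees of freedom, power is 37%, 30% and 20%. At ICC 0 it is 48%. In addition, only health centers are described as randomized, not hospitals.

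**The case against.** The strongest reply is that the allocation really was random and the article says where it came from. That stands. A reader might infer that the study is non-randomized or that the cluster-randomized label is simply false. The documents do not support this: the strategy was allocated by cluster randomization in the parent trial, and the Discussion's phrase is literally true of that trial. The fault is lack of replication combined with purposive selection.

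A reader might also infer that sites were chosen with knowledge of their arm. The article calls the allocation pre-existing but does not date the facility selection, and the only reason it gives is data collection. The confounding does not depend on the order.

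The count of one cluster per arm is derived, and Fig. 1 might show more detail. This is a fair caution, but neither alternative reading rescues the intervention claim.

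Area differences are also partly measured. WBGT outside the home (where feasible) and indoor temperature and humidity are recorded for each woman, activity is measured by accelerometer and diary, and WBGT and occupation are named as model covariates. The two clusters have the same facility types, and women needing admission are excluded. This reduces the confounding but leaves unmeasured area effects.

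Finally, half of the primary objective is the effect of heat itself. The within-woman association is already planned and needs no contrast between areas. That stands, although the sample size rests on the between-group contrast.

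**Conclusion.** The point holds in this form. By the article's own counts there is one purposively selected pair per arm and no between-cluster degrees of freedom. The intervention main effect and the intervention-by-heat interaction therefore cannot be separated from area differences by sample size or by the planned model, and measured covariates help only in part. The 63 per group, and the claim of adequate power with 30% attrition, are valid only for independent women.

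The size depends on the ICC, which is assumed. The chance that area alone produces a 5 bpm difference reaches about 11% only at the highest value used, so it would be wrong to read that as the expected figure. The inflation of type I error is substantial even at ICC 0.01. The conclusion of no degrees of freedom needs no ICC, only the cluster count. It does not follow that the whole study fails: the heat-exposure part of the objective remains estimable.

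**What to change.** - **Study design and Discussion:** describe a sub-study in one purposively selected intervention area and one purposively selected control area of a cluster-randomized trial. State that the between-arm comparison and the intervention-by-heat interaction are exploratory and cannot separate intervention from area effects.
- **Limitations:** add the single pair per arm and its purposive selection.
- **Sample size:** state that the power figure assumes independent women and does not hold for a cluster-level test of the intervention.
- **Main inference:** the within-woman heat to heart-rate association, already planned, can carry it. Making it formally confirmatory is a choice for the investigators, since the present sample size was not derived for it.
- **Optional:** spread the same 200 women over more of the 16 randomized health centers. With 100 analyzed per arm and a t-test on 2(k − 1) degrees of freedom, 5 centers per arm give 81% power at ICC 0.01 and 7 per arm give 82% at ICC 0.02. At ICC 0.05, 8 per arm (all centers, if split evenly) give 75%. Attrition lowers these figures. Ultrasound depends on the hospitals, so this may not be feasible.

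The required changes are to wording only. Their price is a weaker causal claim for the intervention.
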